### Sample size {14}

Ersayli et al. reported that total morphine consumption at 24 h was 13.2 ± 4.1 mg after lumbar discectomy for patients who received local wound infiltration of bupivacaine alone just before incision [14]. The analgesic effect of 1 mg morphine is the same as that of 3.75–7 mg butorphanol. This dose of morphine could be converted into an equianalgesic dose of butorphanol (with conversion factor 1 mg morphine = 3.75–7 mg butorphanol). Therefore, we have estimated that total butorphanol consumption will be about 120.0 ± 90.0 mg at 48 h after laminoplasty or laminectomy for the patients who received preemptive analgesia with local anesthetics.

Nakai et al. suggested that local wound infiltration by addition of betamethasone could reduce the dose of analgesics by about 45% in the 24 h after lumbar discectomy [18]. Therefore, we hypothesize that the cumulative butorphanol consumption during the 48 h after lumbar discectomy will be 120.0 ± 90.0 mg in the control group and 70.0 ± 50.0 mg in the treatment group. Based on a 90% power with a two-sided α of 0.05 and a dropout rate of 20%, we have calculated that at least 116 patients (58 per group) will be required.

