### Trial design {8}

The PRE-EASE trial is a prospective, randomized, open-label, blinded endpoint (PROBE), single-center clinical study designed to compare the postoperative analgesic efficacy of preemptive wound infiltration of ropivacaine alone and betamethasone plus ropivacaine for laminoplasty or laminectomy. In total, 116 patients will be randomly assigned to the betamethasone-ropivacaine (treatment) group and the ropivacaine (control) group at a 1:1 ratio. The Consolidated Standards of Reporting Trials (CONSORT) patient flow diagram is presented in Fig. 1.

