#### Additional interventions

The ongoing continuous infusion of propofol and remifentanil will be stopped right after the suture of the incision. To prevent postoperative nausea and vomiting, 8 mg of ondansetron will be administered. Any residual muscle relaxation will be antagonized by atropine and neostigmine. Once the patient is hemodynamically stable, along with the recovery of adequate spontaneous ventilation and satisfactory neurological evaluations, the patient will be extubated and transferred to a post-anesthesia care unit. A PCA device containing 10 mg butorphanol tartrate injection (HengRui Medical Co., Ltd., Lianyungang, Jiangsu, China) and 10 mg tropisetron hydrochloride injection (Southwest Pharmaceutical Co., Ltd., Chongqing, China) diluted to a total volume of 100 ml with 0.9% normal saline, will be connected to the patients, for a total duration of 48 h. Apon® electronic infusion pumps (ZZB-I-150, Apon Medical Technology Co., Ltd., Jiangsu, China) will be used for patient-controlled analgesia (PCA). The PCA device will have a bolus dose of butorphanol set at 0.3 mg with a lockout interval of 15 min. Both the initial dose and background infusion of the PCA device will be set at zero. The participants will be advised to push the analgesic demand button when they feel pain. Each press will be recorded by an electronic memory system, including both valid and invalid presses. Invalid presses refer to presses for bolus during the lockout period. In case of inadequate analgesia four times after the butorphanol bolus, the bolus dose would be increased gradually with the final maximum dose not exceeding 4 mg per hour. There will be real-time updates of drug dosage, press counts, and time of each press to the iPainfree online recording system. Participants will be allowed to take oral supplementary acetaminophen 500–1000 mg every 4 to 6 h if necessary after 48 h, until the end of our study.

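### The sample size assumes 48-h butorphanol doses that do not fit the PCA device described, so the 90% power is unsupported, though not shown to be too low

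*Protocol article*

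**What the plan says.** Sample size {14} takes 13.2 ± 4.1 mg of morphine in 24 h from a cited discectomy study and converts it on the statement that "The analgesic effect of 1 mg morphine is the same as that of 3.75–7 mg butorphanol". It arrives at 48-h butorphanol of "120.0 ± 90.0 mg in the control group and 70.0 ± 50.0 mg in the treatment group". It then states "Based on a 90% power with a two-sided α of 0.05 and a dropout rate of 20" per cent, and concludes that "at least 116 patients (58 per group) will be required".

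The Primary outcome section defines the endpoint as the cumulative 48-h dose given through the PCA device, so the limits of the device are limits on the endpoint.

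Additional interventions describes that device: "A PCA device containing 10 mg butorphanol tartrate injection", connected for 48 h, with initial dose and background infusion at zero. "The PCA device will have a bolus dose of butorphanol set at 0.3 mg with a lockout interval of 15 min". Strategies to improve adherence {11c} repeats the bolus, lockout and zero background. After repeated inadequate analgesia, "the bolus dose would be increased gradually with the final maximum dose not exceeding 4 mg per hour".

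**The concern.** The planning doses and the pump settings describe the same quantity, and they disagree. Both planned means exceed what the stated bolus and lockout can deliver in 48 h. The target difference of 50 mg is five times the stated content of the device.

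These doses are the only basis given for the trial's size. If demand really were that high, many patients would reach a delivery limit and the observed difference would be compressed. If consumption is really a few milligrams, the absolute means, SDs and 50 mg difference do not describe this trial, and only the implied CVs and relative reduction carry the power. The protocol offers no support for those CVs.

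**Working it through.** **1. Reproducing the stated size.** Inputs from Sample size {14}: means 120 and 70 mg, SDs 90 and 50 mg, two-sided α 0.05, power 90%, dropout 20%. From Trial design {8}: 1:1 allocation.

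- n per arm = (1.960 + 1.282)² × (90² + 50²) / 50² = 44.6, so 45 by the normal approximation.
- By the t test with unequal variances, power is 89.5% at 45 per arm and 90.1% at 46.
- 46 / 0.8 = 57.5, so 58 per arm and 116 in total. The stated figure reproduces.

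**2. What the pump can deliver in 48 h.**

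- Stated settings: 4 boluses/h × 48 h = 192 boluses; 192 × 0.3 mg = 57.6 mg. A dose of 120 mg needs 120 / 0.3 = 400 boluses and 70 mg needs 233.
- Escalation ceiling for all 48 h: 4 × 48 = 192 mg. A mean of 120 mg is then 120 / 48 = 2.5 mg/h on average, against 1.2 mg/h at the stated settings.
- Device content: 120 / 10 = 12 fills; 70 / 10 = 7 fills.

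**3. Whether the control SD is attainable.** For a variable confined to 0 to c with mean m, the largest possible SD is √(m(c − m)). With m = 120 and c = 192 this is √(120 × 72) = 93.0 mg, reached only if every patient takes 0 or 192 mg. An SD of 90 mg is close to that extreme. Mean + 1 SD = 210 mg lies above the ceiling.

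**4. The conversion.** The source dose over 48 h is 2 × 13.2 = 26.4 mg morphine.

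- Multiplying by 3.75–7 gives 99–185 mg, which contains 120 mg.
- Dividing by 7–3.75 gives 3.8–7.0 mg, which fits a 10 mg fill. The planned 120 mg is 17 to 32 times larger (120 / 7.04 and 120 / 3.77).
- SD: 4.1 × 2 × (3.75 to 7) = 31–57 mg, even with the 24-h SD simply doubled. The 90 mg is not derived from it.

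**5. Dependence on scale.** The formula in step 1 uses only ratios. The implied CVs are 90/120 = 0.75 and 50/70 = 0.71, and the reduction is 50/120 = 41.7%. If all doses shrink in proportion, n is still 45 per arm by the normal approximation.

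**6. Sensitivity, 46 evaluable per arm.** The demand distributions below are assumptions, with the planned means and SDs; demand above the cap is cut off at the cap.

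| Cap | Demand | At cap, control / treatment | Mean delivered, control / treatment | t-test power |
|---|---|---|---|---|
| 57.6 mg | gamma | 73% / 51% | 51 / 45 mg | about 48% |
| 57.6 mg | lognormal | 78% / 49% | 54 / 47 mg | about 82–83% |
| 192 mg | gamma | 18% / 3% | 106 / 69 mg | about 90% |
| 192 mg | lognormal | 15% / 3% | 106 / 68 mg | about 95% |

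At the 192 mg cap, Mann-Whitney power is about 86–95% over the two shapes.

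**7. Sensitivity to the CV.** With the same CV in both arms, a 41.7% reduction and the normal approximation, pooled SD (in units of the control mean) = CV × √((1 + 0.583²)/2).

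| CV | n per arm for 90% | Power at 46 per arm |
|---|---|---|
| 0.5 | 21 | 99.8% |
| 0.75 | 46 | 90% |
| 1.0 | 81 | 69% |
| 1.25 | 127 | 50% |

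**The case against.** The strongest reply is that the sample size is not miscalculated. It reproduces, and because only the ratio of difference to SD matters, a wrong conversion factor alone would leave both 116 and 90% unchanged. That stands, and it limits the point. A reader might infer that the trial is underpowered; the document does not show this.

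The second reply is that 57.6 mg is not the protocol's ceiling. The escalation clause allows up to 4 mg/h, both means lie below 192 mg, and power at that cap stays near 90%. This also stands, so the means cannot be called impossible. It does not rescue the control SD, and it would make well above the standard setting the average for a control patient throughout 48 h.

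Two further inferences should be resisted. One is that a single 10 mg fill is all a patient can receive. The article describes no refill, but a 4 mg/h ceiling would empty 10 mg in 2.5 h, so replacement may be presupposed, and an article may leave such logistics out. The other is that the conversion ratio is certainly inverted. The fit of the divided figure with a 10 mg fill is suggestive, but the source of the ratio is not at hand, so this can only be a query.

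Finally, an SD larger than the source's can be defended: 48 h rather than 24 h, two procedures and a varying number of levels. A larger SD is also conservative for n. What remains is that 90 mg is unexplained and hardly attainable at a mean of 120 mg.

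**Conclusion.** The point holds as an unreconciled planning assumption. Both assumed means exceed the 57.6 mg deliverable at the stated settings. Under the most generous reading of the escalation clause, the control SD of 90 mg is within 3 mg of the mathematical maximum. These results use only the protocol's own numbers.

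The consequence is that the 90% power has no demonstrated support; its true value could be higher or lower. Under capped demand, t-test power runs from about 48% to 95%, depending on the cap and the assumed distribution. A reader might infer that the treatment difference would disappear under the lower cap. It would not: in the gamma case, for example, delivered means remain about 51 and 45 mg. If doses are merely mis-scaled, power depends on the CV, with the range in step 7. The protocol does not say which of these situations applies.

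**What to change.** Rewrite the sample-size paragraph as follows.

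- Check the direction of the morphine–butorphanol ratio against its source.
- Reconcile the assumed doses with the PCA settings and drug supply in Additional interventions and Strategies to improve adherence {11c}, and state which delivery limit and supply the figures assume. This review takes no position on which setting or dose is right.
- Give the control mean and SD on a scale that the PCA can deliver, and express the treatment mean as a relative reduction.
- Justify the CV from a named source or from pilot data.
- Restate the power that the planned 116 patients provide, as a range over plausible CVs in the manner of step 7.

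The cost is one paragraph and a power statement that may be less favourable. Whether 116 remains adequate cannot be promised before the CV and the reduction are re-derived.

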### Recruitment {15}

The PRE-EASE trial team includes two research members from the department of neurosurgery who will be in charge of the patient recruitment process.

### Assignment of interventions: allocation

#### Sequence generation {16a}

Eligible participants will be randomly assigned by a computerized random-number list generator used for randomization (SPSS 25.0), after written consent is obtained.

#### Concealment mechanism {16b}

The study investigator will be responsible for preparing the respective drugs to be used for preemptive infiltration. Only the doctors in charge of the postoperative pain evaluation will be blinded, along with the outcome assessors and data analysts.

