### Interventions

#### Explanation for the choice of comparators {6b}

A total of 30 ml of solution will be prepared for each group, which will include 0.5 ml of compound betamethasone injection (Diprospan® betamethasone propionate 5 mg and betamethasone sodium phosphate 2 mg) added to 14.5 ml of saline and 15 ml of 1% ropivacaine (NaiLePin®10 mg/ml, AstraZeneca AB, Södertälje, Sweden) for the treatment group and 15 ml of ropivacaine added to 15 ml of saline for the control group [15, 16]. The study investigator will be responsible for preparing the respective drugs to be used for preemptive infiltration in these two groups, and the neurosurgeon will infiltrate the planned incision site with the respective study solution, prior to the incision.

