#### Anesthesia management

During the preoperative visit, after signing the written consent, patients will be taught how to indicate postoperative pain based on a VAS, with levels ranging from 0 (no pain) to 10 (maximal pain). Patients will also be taught how to use the PCA device. In the operating theater, each patient will be prepared for monitoring of continuous blood pressure and heart rate, peripheral pulse oximetry, bispectral index (BIS system, Covidien/Medtronic, Minneapolis, MN, USA), and electrocardiography. Then a peripheral venous cannula will be inserted and an intravenous (IV) infusion of crystalloid solution will be started. Each participant will be premedicated with an IV infusion of midazolam 0.03 mg/kg before the induction of general anesthesia. A standard general anesthesia protocol will be followed, using 0.3–0.4 μg/kg sufentanil, 1.5–2 mg/kg propofol, and 0.2 mg/kg cisatracurium or 0.6 mg/kg rocuronium. Anesthesia will be maintained with IV administration of propofol and remifentanil, and muscle relaxation will be maintained using IV cisatracurium or rocuronium. After endotracheal intubation, invasive blood pressure will be monitored by placing an arterial line if deemed necessary by the anesthesiologist in charge. Ventilation will be adjusted as needed to maintain normocapnia. Anesthesia will be maintained with IV propofol and remifentanil, and muscle relaxation will be maintained using IV cisatracurium or rocuronium. Local infiltration of the prepared solution will be performed by the neurosurgeon, before the incision is made. Sufentanil will be administered at certain time points to attenuate potent stress responses and maintain the mean arterial pressure and heart rate fluctuations within a 20% range of baseline. No additional analgesics will be administered intraoperatively. Antihypertensive drugs or vasoactive drugs will be administered as needed, and crystalloid and colloid solutions will be infused as necessary, by the anesthesiologist in charge. All intraoperative physical parameters, fluid input and output, and dosage of all drugs will be closely monitored and recorded.

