### Strategies to improve adherence to interventions {11c}

During the study, periodic monitoring will be conducted by a blinded research member, who will visit each patient in person at 2, 4, 8, 24, and 48 postoperative h, for the recording of postoperative parameters and to ensure adherence to interventions. The blinded postoperative care nurses of the neurosurgical department will be checking on patients from time to time and will advise them to press the analgesic demand button on the PCA device if necessary. Preoperatively, the patients will have been instructed on how to use the PCA device after their written consent is obtained. Both groups will have the PCA device bolus dose of butorphanol set at 0.3 mg with a lockout interval of 15 min, with the background infusion set to zero. There will be real-time updates of drug dosage, press counts, and time of each press, which will also help with monitoring and improving adherence. After the initial 48-h postoperative period and until the end of the study, patients will be allowed to take oral supplementary acetaminophen 500–1000 mg every 6 h if necessary. Follow-up will be conducted on day 3, at weeks 1, 2, 4, and 6, and at months 3 and 6 by a blinded research member.

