#### Procedure for unblinding if needed {17b}

The design is open label with only the outcome assessors and data analysts being blinded, so unblinding will not occur.

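### The blind excludes participants, who generate the primary outcome and rate the patient-reported secondary outcomes, although withholding allocation from them would be cheap

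*Protocol article*

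**What the plan says.** Trial design {8} declares the design: "The PRE-EASE trial is a prospective, randomized, open-label, blinded endpoint (PROBE), single-center clinical study". Concealment mechanism {16b} gives an exclusive list: "Only the doctors in charge of the postoperative pain evaluation will be blinded, along with the outcome assessors and data analysts". Who will be blinded {17a} repeats these groups. Procedure for unblinding {17b} gives a shorter list: "The design is open label with only the outcome assessors and data analysts being blinded, so unblinding will not occur". Strategies to improve adherence {11c} adds a further group: "The blinded postoperative care nurses of the neurosurgical department will be checking on patients from time to time", and those nurses advise patients on pressing the button. The research member who visits at 2, 4, 8, 24 and 48 h is also described there as blinded. Participants are named in none of these sections.

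The primary outcome is the PCA butorphanol dose over 48 h. Additional interventions says: "The participants will be advised to push the analgesic demand button when they feel pain". It also sets the initial dose and the background infusion to zero. Under Plans for assessment and collection of outcomes {18a}, the pump records the primary outcome electronically, and the secondary outcomes are described as patient-reported scores gathered by blinded staff.

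On delivery, Anesthesia management places the infiltration after induction and intubation: "Local infiltration of the prepared solution will be performed by the neurosurgeon, before the incision is made". Explanation for the choice of comparators {6b} says: "A total of 30 ml of solution will be prepared for each group". Intervention description {11a} keeps the rest of rehabilitation identical between the arms.

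**The concern.** In an open-label trial with blinded endpoint assessment, the blind protects an endpoint to the extent that the assessor's judgement produces it. Here the assessor's judgement plays no part in the primary outcome: the participant presses and the pump counts. The same holds for VAS, PSS, ODI and WHOQOL-BREF, where staff collect a score that the participant has chosen.

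A participant who knows that a steroid was added may press less and rate pain lower. One who knows that it was not may press more. Either response moves the comparison towards the trial's hypothesis, and no analysis can separate it from a drug effect. A participant who knows the arm can also reveal it to the nurses and assessors whom the protocol wants blinded, at any bedside visit or follow-up contact.

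**Working it through.** **1. Does the primary outcome depend on the participant?** With no initial dose and no background infusion, every PCA dose follows a press. The bolus may be increased after repeated inadequate analgesia, which also depends at least partly on what the participant reports. Logging is electronic. Participant behaviour is therefore an open route for bias, and assessor blinding does not act on it.

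**2. Could participants be kept unaware?** Infiltration is described under general anaesthesia, both arms receive an infiltration, and the prepared volumes match: 0.5 + 14.5 + 15 = 30 ml against 15 + 15 = 30 ml. Aftercare is otherwise identical. Nothing in the described procedure reveals the arm to the participant.

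**3. The plan's own sample size.** Inputs from Sample size {14}: control 120 ± 90 mg, treatment 70 ± 50 mg, two-sided α 0.05, power 90%, dropout 20%.

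- Average SD = √((90² + 50²)/2) = 72.8 mg; difference = 50 mg.
- Normal approximation: n = (1.960 + 1.282)² × (90² + 50²)/50² ≈ 44.6, so 45 per arm.
- t test: 46 per arm (power 90.1%).
- Dropout: 46/0.80 = 57.5, so 58 per arm and 116 in total. The stated figure is reproduced.

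Blinding participants changes none of these inputs.

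**4. Illustration of what expectancy could do.** The documents give no figure for an expectancy effect, so the shift b is an assumption and is shown as a range: 5 to 25 mg, which is 10% to 50% of the planned 50 mg difference. The true drug effect is set to zero.

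- SE = √((90² + 50²)/46) = √230.4 = 15.2 mg.
- False-positive rate = Φ(b/SE − 1.96) + Φ(−b/SE − 1.96).
- Example, b = 10: b/SE = 0.66, giving 0.097 + 0.004 = 0.101.

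| Assumed shift (mg) | SDs 90/50, 46 per arm | SDs 90/90, 46 per arm | SDs 90/50, 58 per arm |
|---|---|---|---|
| 0 | 5% | 5% | 5% |
| 5 | 6.3% | 5.8% | 6.6% |
| 10 | 10.1% | 8.3% | 11.5% |
| 15 | 16.7% | 12.6% | 19.9% |
| 20 | 26.1% | 18.7% | 31.6% |
| 25 | 37.7% | 26.6% | 45.6% |

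The middle column is a sensitivity check, since with no drug effect the treatment arm might keep the control SD. The last column shows that more patients make the problem worse, because a fixed bias is then measured more precisely.

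**The case against.** The strongest reply is that the protocol never says participants will be told their arm. A reader might infer from the open-label wording that they will be. The documents do not support that: allocation follows consent, infiltration is described under anaesthesia, and patients may remain unaware in practice. What stands is that the plan permits disclosure and nowhere forbids it.

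A reader might also conclude that the blinded endpoint gives no protection. That goes too far. Blinded nurses reduce differential prompting to press, blinded assessors and analysts reduce biased collection and analysis, and electronic logging removes recording discretion. Nor are all secondary outcomes exposed in the same way: the Ramsay score is judged by an observer, and vomiting is an observable event. The exposure concerns the primary outcome and the patient-reported scores.

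The illustration can be challenged too. Both arms receive ropivacaine, so the contrast in expectation is with an active comparator and may be small. A larger inflation could be obtained from the relative SD of the cited 24-h morphine figure (4.1/13.2 = 31%), but that is not the plan's SD for 48-h butorphanol, so it is not used here.

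Finally, the open-label design with blinded endpoints is declared, and the Discussion defends it in general terms. It is a design choice, not a contradiction. However, that defence rests on endpoint evaluation by blinded experts, which does not describe a press-driven dose, and it gives no reason for letting participants know their arm. The low cost of the change is an inference from the described procedure. Betamethasone is said to be partly particulate, so the surgeon may recognise the solution; an anaesthetised participant cannot.

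**Conclusion.** The point holds in this form: the plan leaves participants outside the blind although they produce the primary outcome and rate the main secondary ones, and blinding the staff cannot prevent expectancy bias on the participant's side. The bias is possible, not shown. It arises only if participants learn their arm, and its size is unknown. On the stated assumptions (no drug effect, the plan's SDs, 46 evaluable per arm, normal approximation) the false-positive rate would be about 6% for a 5 mg shift and about 38% for a 25 mg shift. Because the described procedure already makes participant blinding feasible, this is a cheap improvement that is well worth making. The blinding statements also need aligning in their own right, since the exclusive lists in {16b} and {17b} omit the nurses whom {11c} calls blinded.

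**What to change.** - State that allocation is not disclosed to participants until the 6-month follow-up is complete.
- Bind those who know the arm, namely the surgeon and the investigator who prepares the solution, to non-disclosure. The neurosurgeons also recruit, so this needs to be explicit.
- Add participants, and the nurses already described as blinded, to the list of who is blinded.
- Align the Abstract (Methods), Trial design {8}, Strategies to improve adherence {11c}, Concealment mechanism {16b}, Who will be blinded {17a}, Procedure for unblinding {17b} and the Discussion, so that none still describes the participant as open label.
- Add an emergency unblinding route to {17b}.
- Record the participant's guess of allocation at 48 h, so that the success of the blind can be reported.

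The cost is a change to the consent wording, a protocol amendment to the approved version and a code-break procedure. No extra staff or visits are needed, and the sample size stays at 116 (58 per group).
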